## Ethical and regulatory aspects

The study received ethical approval from East of England – Cambridge South Research Ethics Committee on 15-Mar-2021 (ref: 21/EE/0017) and has Health Research Authority (IRAS 282284) and UK Medicines and Health Care Product Regulatory Agency (MHRA) approvals. Southampton Clinical Trials Unit (SCTU), a Cancer Research UK core funded and UK Clinical Research Collaboration registered Clinical Trials Unit (CTU), is coordinating the trial. A list of recruiting sites can be obtained from the SCTU. The University of Southampton is the sponsor for the trial and is responsible for all legal requirements of conducting a non-commercial clinical trial of an investigational product. The drug for this trial is provided by Bristol Myers-Squib (BMS) who are responsible for the Good Manufacturing Practice quality drug and who is also providing research funding.

The ELEVATE Trial Management Group (TMG) is responsible for overseeing the progress of the trial, including both the clinical and practical aspects. The Chair of the TMG will be the Chief Investigator of the trial. The TMG includes representatives with expertise in oncology, radiology, translational science and medical statistics; as well as being supported by a Patient and Public Involvement contributor and CTU staff involved in the day-to-day running of the trial. An independent Trial Steering Committee has also been established, and an independent DMEC comprising three clinicians and a statistician experienced in this research area (but not directly involved in this trial apart from DMEC membership) has been set up. The aim of the independent DMEC is to safeguard the interests of trial participants, monitor the main outcome measures including safety and efficacy, and monitor the overall conduct of the trial. Charters for these groups are available via [contact] .

The SCTU has undertaken a risk assessment for the ELEVATE trial, which includes the requirements for monitoring (both central and site). The SCTU undertakes several internal audits of its own systems and processes annually and has routine audits from both its sponsor and the independent MHRA every 2-3 years.

## Study participants

The ELEVATE trial is currently recruiting patients with advanced unresectable previously treated oesophagogastric adenocarcinoma with MGMT methylation for which the use of TMZ followed by nivolumab is clinically appropriate treatment in the view of the local principal investigator. The previous treatment must include at least 3 months of platinum and fluoropyrimidine based chemotherapy for advanced disease (see Table 3 for full eligibility criteria). No other investigational medicinal products should be received whilst on study. Immunosuppressive agents, immunosuppressive doses of systemic corticosteroids, concurrent anti-neoplastic therapy and live vaccinations are prohibited during the study. Caution must be used with ototoxic or nephrotoxic concomitant drugs and herbal medication should be stopped prior to study enrolment.

**Table 3 Tab3:** Eligibility Criteria for the ELEVATE Trial

Inclusion Criteria
1. Participants 18 years of age
2. Pathologically confirmed advanced unresectable or metastatic OGA
3. MGMT methylation on archival tissue
4. Mismatch repair proficient (MSI-normal or MMR intact)
5. Previously treated with at least 3 months of platinum and fluoropyrimidine based chemotherapy for advanced disease, without evidence of disease progression
6. Measurable disease per RECIST 1.1 guidelines
7. ECOG Performance Status of 0 or 1
8. Can swallow TMZ capsules
9. Adequate organ function assessed within 7 days before randomisation:
∙ White blood cell count (WBC) > 1.5 X 10^9^/L
∙ Absolute neutrophil count (ANC) > 1.5 X 10^9^/L
∙ Platelets 100 X 10^9^/L
∙ Haemoglobin 90 g/l
∙ Measured/calculated creatinine clearance 60 mL/min (according to Cockroft-Gault formula)
∙ Total bilirubin within normal limits (if patient has documented Gilbert’s disease 1.5 X ULN or direct bilirubin 1.5 X ULN)
∙ Aspartate transaminase (AST) and/or alanine transaminase (ALT) 1.5 X ULN
10. All toxicities (except alopecia, and grade 2 fatigue, neuropathy and lack of appetite/nausea) attributed to prior anti-cancer therapy must have resolved to grade 1 (NCI CTCAE version 5.0) or baseline before administration of study drug
11. Women of childbearing potential (WOCBP) may be included following a confirmed menstrual period and must have a negative serum or urine pregnancy test (minimum sensitivity 25 IU/L or equivalent units of human chorionic gonadotropin (HCG)). The pregnancy test must be within 24 hours prior to starting treatment
12. WOCBP should use one highly effective and one effective method of birth control during the study treatment period and for at least 5 months after the last dose of study treatment
13. Female subjects who are breastfeeding should discontinue nursing prior to the first dose of study treatment and until 5 months after the last dose of study treatment
14. Men who are sexually active with a WOCBP must adhere to contraception during and for a period of 7 months after the last dose of study treatment
15. Absence of any psychological, familial, sociological or geographical conditions potentially hampering compliance with the study protocol and follow-up schedule; those conditions should be discussed with the patient before registration in the trial
16. Written informed consent
Exclusion Criteria
1. Previous treatment with TMZ
2. Prior treatment with an anti-PD-1, anti-PD-L1, anti-PD-L2, anti-CD137, or anti-CTLA-4 antibody, or any other antibody or drug specifically targeting T-cell co-stimulation or immune checkpoint pathways
3. Active central nervous system metastases
4. Candidate for curative surgery
5. Previous malignancies are excluded unless a complete remission was achieved at least 5 years prior to study entry. Adequately treated cervical carcinoma in situ, and localised non-melanoma skin cancer are not exclusion criteria, regardless of timepoint diagnosis
6. Active, known, or suspected infectious or autoimmune disease (except for patients with type 1 diabetes mellitus, residual hypothyroidism due to autoimmune thyroiditis only requiring hormone replacement, skin disorders (such as vitiligo, psoriasis, or alopecia) not requiring systemic treatment are permitted to enrol)
7. Conditions requiring systemic treatment with either corticosteroids (10 mg daily prednisolone or equivalent) or other immunosuppressive medications within 14 days of study drug administration
8. Interstitial lung disease
9. > Grade 1 peripheral neuropathy
10. Positive test result for HBV or HCV indicating acute or chronic infections
11. Known history of testing positive for HIV or known AIDS
12. Known hypersensitivity to the components or excipients of co-trimoxazole, temozolomide or nivolumab
13. Known hypersensitivity to dacarbazine (DTIC)
14. Clinically significant abnormal 12-lead ECG. If clinically indicated, cardiac function assessment using either echocardiography or MUGA Scan, if clinically significant the patient is ineligible
15. In the past 6 months serious cardiac illness or medical condition including but not confined to:
∙ History of documented CHF
∙ High-risk uncontrolled arrhythmias
∙ Angina pectoris requiring antianginal medication
∙ Clinically significant valvular heart disease
∙ Evidence of transmural infarction
∙ Poorly controlled hypertension (e.g. systolic >180mm Hg or diastolic > 100mm Hg)
16. Patients with severe liver parenchymal damage
17. Patients with severe renal insufficiency where repeated measurements of the plasma concentration cannot be performed
18. Patients with a history of drug-induced immune thrombocytopenia with use of trimethoprim and/or sulfonamides
19. Patients with acute porphyria
20. Patients with severe myelosuppression

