During continuous dose TMZ, the participants’ FBC should be checked weekly. TMZ can continue, providing the following conditions are met: 
Absolute Neutrophil Count (ANC) 1.5 x 10^9^/lThrombocyte count 100 x 10^9^/lCommon toxicity criteria (CTC) non-haematological toxicity Grade 1 (except for alopecia, nausea and vomiting).

Table 2 details the criteria for modifying the continuous dosing of temozolomide.

**Table 2 Tab2:** Dose modifications for continuous dosing temozolomide

Toxicity	Withhold TMZ (until counts return to above criteria)	TMZ discontinuation
ANC	0.5 and < 1.5 x 10^9^/l	< 0.5 x 10^9^/l
Platelets	10 and < 100 x 10^9^/l	< 10 x 10^9^/l
CTCAE toxicity (version 5)	Grade 2	Grade 3-4

While dose modifications are not permitted on this trial, there are a set of criteria that should be assessed when considering delaying, discontinuing or restarting nivolumab treatment in relation to adverse events and infusion related events (Additional file 1 explains these criteria in more detail).

Participants on IV steroids may be switched to an equivalent dose of oral corticosteroid (e.g. prednisolone) at start of tapering or earlier, once sustained clinical improvement is observed. Lower bioavailability of oral corticosteroids should be considered when switching to the equivalent dose of oral corticosteroids.

Prophylactic antibiotics should be considered in the setting of ongoing immunosuppression.

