## Statistical analysis

For the primary and secondary objectives, patients who have consented and received at least one dose of nivolumab will be analysed. However, for the exploratory objectives those that have just received TMZ, and not commenced onto nivolumab, will also be analysed.

Response rates (including the primary endpoint) and other categorical data will be presented as percentages with 95% Clopper-Pearson confidence Intervals [37], with continuous data as means and standard deviations or medians and quartiles as appropriate. The primary endpoint will also be presented with a one-sided 90% lower confidence interval limit (to align with the sample size calculation). A secondary analysis will be conducted for the primary endpoint using only those who receive at least two weeks of TMZ (to acknowledge that this subgroup should have been exposed sufficiently for the proposed TMZ mechanisms to have had an impact). Time to event data will be presented in a Kaplan-Meier curve with median survival rates being presented. Waterfall plots will be produced to show changes in tumour size from baseline to treatment assessment time points.

A full and detailed statistical analysis plan will be developed prior to the final analysis of the trial.

All analyses will be carried out using STATA v16 or higher and/or SAS v9.4 or higher.

There are no plans for an interim analysis to be conducted during the ELEVATE trial.

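### Inclusion 10 conflicts with exclusion 9 on grade 2 neuropathy, and admits grade 2 fatigue and appetite loss that, read literally, meet the rule for withholding TMZ

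*Protocol article*

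**What the plan says.** Four places in the protocol article bear on this.

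- **Table 3, inclusion 10** sets the entry standard for residual toxicity: "All toxicities (except alopecia, and grade 2 fatigue, neuropathy and lack of appetite/nausea) attributed to prior anti-cancer therapy must have resolved to grade 1".
- **Table 3, exclusion 9** excludes patients with "> Grade 1 peripheral neuropathy", with no reference to cause.
- **Treatment, conditions during continuous TMZ.** The list opens with "TMZ can continue, providing the following conditions are met". Its last item is "non-haematological toxicity Grade 1 (except for alopecia, nausea and vomiting".
- **Treatment, Table 2.** The row labelled "CTCAE toxicity (version 5" puts grade 2 in the column headed "Withhold TMZ (until counts return to above criteria" and grade 3-4 in the discontinuation column.

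Two further statements give the context. Inclusion 5 requires of every participant "Previously treated with at least 3 months of platinum and fluoropyrimidine based chemotherapy for advanced disease, without evidence of disease progression". The Statistical analysis section defines the set for the primary and secondary objectives: "patients who have consented and received at least one dose of nivolumab will be analysed". That set has no minimum TMZ exposure. A secondary analysis of the primary endpoint is limited to participants with at least two weeks of TMZ.

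**The concern.** A site that screens a patient with grade 2 peripheral neuropathy from earlier chemotherapy gets two answers from one table. A site that enrols a patient with grade 2 fatigue or appetite loss, as inclusion 10 allows, then meets a treatment rule that does not recognise the allowance.

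Two things are at stake. The first is consistency and safety: if sites interpret the rules differently, similar patients will be enrolled, dosed and held differently. The second is what the trial tests. The hypothesis is that TMZ primes the tumour for nivolumab. Under the Treatment section, participants move on to nivolumab after 3 months of TMZ, progression or withdrawal from TMZ, and one nivolumab dose is enough to be analysed. A participant whose TMZ was held for most of the priming period would therefore count among the 18 in the same way as one who received it in full.

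**Working it through.** **1. Passages side by side**

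| Residual grade 2 symptom from prior therapy | Inclusion 10 | Exclusion 9 | TMZ continuation list | Table 2, CTCAE row |
|---|---|---|---|---|
| Peripheral neuropathy | allowed | excluded | not exempt | withhold |
| Fatigue | allowed | silent | not exempt | withhold |
| Lack of appetite | allowed | silent | not exempt | withhold |
| Nausea | allowed | silent | exempt | withhold (no exception printed) |

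- *Neuropathy.* A patient must meet every inclusion criterion and no exclusion criterion, so exclusion 9 decides. The exemption in inclusion 10 could then apply only to non-peripheral neuropathy, and nothing in the text says that this was meant.
- *Fatigue and appetite loss.* These pass entry, fail the continuation condition and fall in the withhold column. No wording restricts the rule to toxicity that is new, worse than at baseline or attributed to TMZ.
- *Nausea.* Entry and continuation text agree. Only the shortened table row differs.

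The comparison sign before grade 1 in the continuation list is not legible in the text at hand. This does not matter, because Table 2 places grade 2 under withholding.

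**2. The plan's own design figures**

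Inputs from Sample size and recruitment: n = 18, success at 4 or more responses, 10% and 30% response rates, 10% alpha, 80% power. With X binomial:

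- Alpha = 1 − P(X ≤ 3 | 18, 0.10) = 1 − 0.9018 = 0.098
- Power = 1 − P(X ≤ 3 | 18, 0.30) = 1 − 0.1646 = 0.835

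The smallest n that meets both targets is 18, so the stated design reproduces. This point disputes no figure in it.

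**3. Illustration of dilution (assumed response rates)**

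Suppose k of the 18 get no effective priming and respond at 10%, while the other 18 − k respond at 30%. Then

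Power(k) = Σₐ C(k,a) · 0.1ᵃ · 0.9ᵏ⁻ᵃ · P[Bin(18 − k, 0.3) ≥ 4 − a], for a = 0 to k.

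For k = 2: 0.81 × 0.7541 + 0.18 × 0.9006 + 0.01 × 0.9739 = 0.783.

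| Unprimed of 18 | 0 | 1 | 2 | 3 | 4 |
|---|---|---|---|---|---|
| Power | 0.835 | 0.811 | 0.783 | 0.752 | 0.718 |

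The loss is 0.835 − 0.783 = 0.052 with two participants and 0.835 − 0.718 = 0.117 with four.

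**The case against.** The other side has several fair arguments.

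- **The neuropathy conflict resolves itself.** Exclusion 9 screens these patients out. This stands as a limit on the consequence: they cannot be among the 18 if both criteria are applied. One criterion still does not do what it says.
- **The continuation list is not a start rule, and toxicity in a TMZ table can be read as toxicity arising on TMZ.** That reading is reasonable, but the text does not state it, so the literal reading is equally open to a site.
- **Grade 2 means withhold, not discontinue.** Correct. A reader might infer that eligible participants lose TMZ permanently from the start; the documents do not say that. For a persistent symptom, however, the hold has no clear end, because the restart wording refers to counts.
- **Table 2 is only abbreviated.** Neutrophils and platelets have their own rows, and the withhold column points back to the list above it. This largely stands, so the mismatch between table and text is minor.
- **Low exposure is already anticipated**, both by the route to nivolumab after TMZ withdrawal and by the two-week secondary analysis. This covers part of the effect on interpretation. It does not reconcile the rules, and the primary analysis is unchanged.
- **The article condenses a fuller protocol, and toxicity guidance sits in Additional file 1, which is not shown.** Handling of baseline grades may be explained there. The printed passages still disagree with one another.

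A reader might also infer that residual toxicity after platinum is common enough for under-primed participants to decide the result against a threshold of 4. The documents do not support this. They give no frequency, inclusion 7 limits entry to ECOG 0 or 1, and the neuropathy group drops out through exclusion 9.

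**Conclusion.** The inconsistencies are real and can be checked by reading alone. Inclusion 10 and exclusion 9 disagree on grade 2 peripheral neuropathy. Grade 2 fatigue and lack of appetite are permitted at entry but, read literally, meet the criterion for withholding TMZ.

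The statistical effect is uncertain and probably moderate. The number affected is not given. The power figures rest on an extreme assumption, that affected participants gain nothing from TMZ and respond at the uninteresting rate of 10%. Under it, two affected participants take power just below the stated 80%, and four cost about 12 percentage points. The direction is towards missing a real effect. If all 18 respond at 10%, the false-positive rate stays at 0.098.

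The correction is worth making mainly for uniform eligibility, dosing and safety across sites, while recruitment is under way.

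**What to change.** Reconcile the passages in a short clarification:

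1. Make inclusion 10 and exclusion 9 agree on grade 2 neuropathy.
2. State whether the TMZ continue and withhold conditions apply to symptoms already present and permitted at entry, or only to change from baseline.
3. As a minor point, give the CTCAE row of Table 2 the same scope and exceptions as the text.

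The clinical team decides which version holds in each case. The cost is a brief amendment and a notice to sites. Sample size and data collection do not change.

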### Withdrawal criteria

Participants are free to withdraw consent from the study at any time without providing a reason. A participant could also withdraw from receiving study treatment but may not wish to withdraw from the trial. In this instance, the participant will be encouraged to attend follow-up visits in accordance with the trial schedule. Should any participant become pregnant during the trial, study treatment will be discontinued.

After the participant has entered the trial, the clinician remains free to give alternative treatment to that specified in the protocol at any stage if they feel that it is in the participant’s best interest, but the reasons for doing so should be recorded. In these cases, participants will be withdrawn from protocol treatment but remain within the trial for the purposes of follow-up and data analysis. All participants are free to withdraw at any time from the protocol treatment without giving reasons and without prejudicing further treatment.

## Study procedure

### Tumour analysis consent

There will be a two-stage consent process for participation in the ELEVATE trial. Stage 1 will ask the patient to consent for their archival tumour or resection sample, collected at diagnosis, to be analysed. The sample will be sent to the central laboratory. Should the analysis show MGMT methylation, the patient will be asked if they wish to participate in the main trial. Before consent is obtained, the patient will be given a full explanation of this stage of the trial and offered a Patient Information Sheet (PIS). Patients can consent to stage 1 by phone (sending the Stage 1 Informed Consent Form (Additional file 2) by post to the research office) or in person. To be eligible to consent to stage 1, patients must have: 
Any advanced OG cancer, planned to be treated or being treated, with at least 3 months of platinum and fluoropyridine based chemotherapyArchival tumour tissue available to be sent to the central laboratory for analysis

### Main trial consent

If MGMT methylation is confirmed, the patient will be asked to consent to the main trial. Consent to enter the main trial will be sought from each participant only after a full explanation has been given, a PIS offered and time allowed for consideration. Signed participant consent will be obtained, using the trials Informed Consent Form (Additional file 3), within a hospital setting. The process will be documented in the patient’s medical records. Only site staff named on the Delegation Log and authorised to do so may obtain consent. Patients may refuse to participate without giving reasons and this will not prejudice their future treatment.

The trial’s Informed Consent Form detail the consent provisions for collection and use of participant data and biological specimens in future research (Additional files 2 and 3).

### Screening

Following informed consent for the main trial, assessments including a physical examination, full blood count, serum biochemistry, including renal, liver and bone profiles, HBV, HCV and HIV serology, and endocrine tests (morning cortisol, ACTH, TSH (Free T3 and Free T4 in case of abnormal TSH)) are completed within 28 days prior to TMZ treatment commencing, with a CT scan being undertaken to assess the disease according to RECIST v1.1. Concomitant medication and medical history will be recorded. In addition, women of childbearing potential (WOCBP) will undertake a pregnancy test. An ECG will be carried out, as will an Echo/MUGA, if clinically indicated. Bloods for translational research will also be collected during screening.

### Treatment and follow-up visits

Participants attend hospital appointments for treatment cycles with assessments similar to those performed during screening, plus reviews of adverse events and treatment adherence. The investigator and/or study personnel will phone participants to check for adherence and toxicities to TMZ, and participants will also have weekly FBC. The time schedule of enrolment, interventions, assessments, and visits for participants are fully detailed in the schedule of events (Table 1). Participants completing the trial, defined as progression on nivolumab (following iRECIST criteria), unacceptable toxicity, withdrawal of consent, or the maximum treatment duration of 24 months on nivolumab, will be managed by standard clinical care from their usual treating clinician. Following confirmed progression patients will be followed up remotely every 4 weeks (via a patient notes check or phone call if required) for details of next treatment and survival until the last participant has completed the study.

Serious adverse event reporting occurs in real-time to the SCTU safety desk throughout the study. Serious adverse events are assessed to determine whether they are related to drug treatment and unexpected or not, and subsequently reported to both Bristol Myers Squibb and the UK regulatory bodies.

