Endocrine tests: Morning cortisol, ACTH, TSH (Free T3 and Free T4 in case of abnormal TSH)		X				X^j^	
Full blood count		X	X^k^	X^k^	X	X^k^	
Serology – HBV or HCV		X					
ECG^l^		X					
Adverse Events		X	X	X	X	X	X
Concomitant Medication		X^m^	X	X	X	X	X
Patient registered with NHS Digital			X				
Quality of Life Questionnaires^n^			X	X	X	X	X
Details of next treatment							X
TRANSLATIONAL SAMPLES							
Tumour Biopsy (endoscopy)					X		X^o^
Translational blood (ctDNA, Plasma)		X	X	X^p^	X	X^q^	X

^a^Height and weight. Height only required at screening

^b^Temperature, blood pressure, heart rate, respiratory rate, oxygen saturation

^c^If clinically indicated

^d^Assessments performed following RECIST 1.1/iRECIST guidelines as appropriate)

^e^CT scans are required at week 6 and week 12 of TMZ treatment. Assessment of scan should be completed following RECIST 1.1 guidelines

^f^CT scan not required if cessation of TMZ occurs within 4 weeks of the week 6 scan

^g^CT scan at week 6 and week 12 of Nivolumab treatment and then every 12 weeks thereafter until CT scan demonstrates unconfirmed progression, following iRECIST guidelines, then a confirmatory CT scan should be performed 4-6 weeks later

^h^Urea and electrolytes

^i^AST and/or ALT, ALP, bilirubin

^j^Every 6 weeks on nivolumab (TSH, cortisol)

^k^FBC weekly whilst on TMZ

^l^Within 7 days prior to treatment start date

^m^To include all those being taken from 30 days prior to starting trial treatment and during treatment and up to 100 days after last study dose

^n^EORTC QLQ-C30, EQ-5D-5L & QLQ-OG25

^o^Optional endoscopy

^p^At 4-6 weeks from D1 C1 TMZ

^q^At 4-6 weeks from D1 C1 Nivolumab

There will be no dose escalations or reductions of nivolumab allowed. Participants may be dosed no less than 12 days from the previous dose. The infusion will be administered through a sterile, non-pyrogenic, low protein binding in-line filter with a pore size of 0.2-1.2 *μ*m. It will not be administered as an intravenous push or bolus injection. The total dose may be infused directly as a 10 mg/mL solution or can be diluted to as low as 1 mg/mL with sodium chloride 9 mg/mL (0.9%) solution for injection or glucose 50 mg/mL (5%) glucose solution for injection. The infusion will be administered over 30 minutes. After administration the line will be flushed with sodium chloride 9 mg/mL (0.9%) solution for injection or 50 mg/mL (5%) glucose solution for injection.

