### Sample size and recruitment

The sample size calculation was performed using Sample Size Tables for Clinical Studies. This phase II trial will be based on A’Hern’s single stage design [36]. The primary endpoint of objective response measured in ELEVATE is to nivolumab (following progression, or 3 months without progression, on TMZ), not to TMZ monotherapy, i.e., the baseline measurement for indicating response/progression is taken from the point of initiation of nivolumab.

Based on 10% alpha and 80% power, and assuming a response rate of <10% would not be sufficient activity to warrant further investigation in a future phase III, and a >30% response rate would warrant further investigation in a future phase II, the required sample size is 18. If 4 or more responses are observed in 18 patients then the treatment will be considered sufficiently active to justify its inclusion in a future phase III. The lower limit of 10% ORR was chosen based on this being expected when using nivolumab in unselected populations.

In order to identify 18 MGMT low/methylated patients and based on an estimated minimum 20% showing MGMT loss then, 90 patients will be required to be screened. We anticipate needing to screen approximately 120 patients to account for screen failures and a very small number of deaths in recruited participants prior to starting nivolumab.

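### The article conflicts on trial status and CT after a toxicity stop, so a participant leaving nivolumab before week 6 can be analysed for response without any protocol-required scan.

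*Protocol article*

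**What the plan says.** All references are to the protocol article.

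- **Treatment and follow-up visits** defines who has finished: "Participants completing the trial, defined as progression on nivolumab (following iRECIST criteria), unacceptable toxicity", together with withdrawal of consent and the 24-month limit. These participants pass to standard care from their usual clinician. Four-weekly remote follow-up is described only after confirmed progression.
- **End of the trial** likewise equates the last participant's end of nivolumab with completing the trial, and lists unacceptable toxicity among the reasons for stopping.
- **Withdrawal criteria** says of someone who leaves treatment but not the trial that "the participant will be encouraged to attend follow-up visits in accordance with the trial schedule". Someone whom the clinician moves to another treatment also stays in for follow-up and analysis.
- **Table 1**: the CT row is blank under Progression/End of treatment. Footnote g, attached to the nivolumab-cycle column, reads "CT scan at week 6 and week 12 of Nivolumab treatment and then every 12 weeks thereafter". The sentence then continues: scanning runs until a CT shows unconfirmed progression, with a confirmatory scan 4-6 weeks later.
- **Statistical analysis** sets the primary population: "patients who have consented and received at least one dose of nivolumab will be analysed". No scan is required for inclusion.
- **Setting** aims for up to 18 evaluable patients and does not define evaluable.

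**The concern.** The primary endpoint is best response to nivolumab, with the baseline reset at the start of nivolumab, so scans from the temozolomide phase cannot supply it. It needs at least one CT after that point. Whether a participant who stops early for toxicity gets one depends on which section a site follows. One site could regard the participant as having completed the trial and schedule nothing more. Another could keep to the trial schedule and obtain the week 6 and week 12 scans.

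Both participants would be analysed. In the first case a response that appeared after a short exposure might go unrecorded because of a visit rule, not because of the tumour. The gap would be concentrated in participants with early toxicity. With success set at four responses, one or two such participants matter.

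An analysis plan can decide how to score a participant with no scan. It cannot recover a scan that nobody was asked to take.

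**Working it through.** **Step 1. Who can be unscanned.** Nivolumab is given every 2 weeks, so doses on schedule fall at weeks 0, 2 and 4 before the first CT at week 6. A permanent stop after one, two or three doses therefore comes before that CT. If stopping is completion, no later CT is required. A participant who stops between weeks 6 and 12 already has one scan that can record a response, and is not counted below.

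**Step 2. Does a toxicity stop fall under both rules?** Withdrawal criteria does not name toxicity. The Treatment section, however, gives toxicity as an example of withdrawal from temozolomide. Its list of reasons for ending nivolumab has no separate toxicity item, only progression, the 24-month limit, death, and withdrawal from treatment or study. A toxicity stop on nivolumab can reasonably be read as a withdrawal from treatment, and so falls under both sections.

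**Step 3. Reproduce the stated design.** Inputs, all from Sample size and recruitment: "Based on 10% alpha and 80% power"; null rate 0.10, from "assuming a response rate of <10% would not be sufficient activity"; target rate 0.30, from "a >30% response rate would warrant further investigation"; success rule, "If 4 or more responses are observed in 18 patients".

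P(X ≥ 4 | n, p) = 1 − Σ (x = 0 to 3) C(n, x) p^x (1 − p)^(n − x)

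- n = 18, p = 0.10: 1 − (0.1501 + 0.3002 + 0.2835 + 0.1680) = 0.098
- n = 18, p = 0.30: 1 − (0.0016 + 0.0126 + 0.0458 + 0.1046) = 0.835

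Eighteen patients with four responses is the smallest exact design meeting 10% and 80%. The sample size is correct.

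**Step 4. Effect of unscanned participants.** Suppose k of the 18 have no CT on or after nivolumab and count as non-responders, with the rule still four responses. A response can then be seen in only 18 − k, so the probability is P(X ≥ 4 | 18 − k, p). The values of k are assumed; the article gives no rate of early toxicity stops.

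| k | Participants scanned | Type I error (p = 0.10) | Power (p = 0.30) | Power lost (points) |
|---|---|---|---|---|
| 0 | 18 | 0.098 | 0.835 | 0 |
| 1 | 17 | 0.083 | 0.798 | 3.7 |
| 2 | 16 | 0.068 | 0.754 | 8.1 |
| 3 | 15 | 0.056 | 0.703 | 13.2 |

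**Step 5. The same effect as a rate.** If each participant independently has probability d of being unscanned, unrelated to response, the observable response rate is 0.30(1 − d). With n = 18, power is 0.799, 0.758, 0.711 and 0.659 for d = 5%, 10%, 15% and 20% (also assumed).

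**Step 6. Is there an allowance?** The screening figure of about 120 covers screen failures and a very small number of deaths before nivolumab. It does not mention early stops after the first nivolumab dose.

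**The case against.** A reader might infer that a participant who stops early for toxicity will certainly have no scan, so that any later response is never measured. The article does not support that, for four reasons.

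- Footnote g ends CT at unconfirmed progression, not at the last dose. It can be read as keeping the scans going after a stop.
- Standard care does not mean no imaging. Ionising radiation says that all but two of the trial scans are standard of care. Such scans may exist, although nothing requires or times them, or says that they reach the trial database.
- Withdrawal criteria only encourages attendance and does not name toxicity, so the conflict rests on the inference in Step 2.
- Nivolumab can be delayed and restarted, so a participant with few doses may still be on schedule at week 6.

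The blank CT cell is also weak evidence by itself, because progression is established by a CT in any case.

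The number unscanned is hypothetical, and one such participant leaves power only 0.2 points under 80%. If evaluable in Setting means having a scan, these participants might not count towards the 18, although Statistical analysis would still include them. The full protocol, the analysis plan and the additional file on nivolumab discontinuation are not shown and may settle some of this.

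These points reduce the finding from a certain loss of scans to a conflict between sections. They do not remove it. Footnote g also counts weeks of nivolumab treatment and belongs to the nivolumab-cycle column, while two sections treat the end of nivolumab as the end of participation. Two sites could each follow the text in good faith and act differently.

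**Conclusion.** The sections conflict on trial status and tumour assessment after a toxicity stop. If Treatment and follow-up visits and End of the trial are followed as written, a participant who stops permanently before week 6 has no protocol-required CT on or after nivolumab, yet belongs to the primary analysis.

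The cost is up to 13 points of power: 83.5% becomes 79.8%, 75.4% or 70.3% with 1, 2 or 3 unscanned. This rests on three assumptions: those numbers, no usable standard-care scan, and scoring as non-response. Type I error falls from 0.098 to 0.083, 0.068 or 0.056, so the danger is passing over an active regimen, not a false success. The sample size and the four-response rule are sound. This is a cheap improvement, not a flaw that invalidates the design.

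**What to change.** Reconcile Withdrawal criteria, Treatment and follow-up visits, End of the trial and Table 1 footnote g:

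1. Separate end of treatment from completion of the trial, so that stopping nivolumab without progression does not in itself end participation.
2. State in footnote g that the existing CT schedule is timed from the first nivolumab dose. It should continue after a stop without progression until progression, new anti-cancer therapy or withdrawal of consent.
3. Adjust the end-of-trial definition, which now closes the trial when the last participant finishes nivolumab and would cut off such scans.

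The cost is a wording amendment, a few additional scans and slightly longer follow-up for a few participants. The change concerns outcome assessment only; no view is taken on when treatment should stop.
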